**1. Context**

**1.1. Current protocols for the treatment of HAT - Toxicity of melarsoprol.**

## Standard protocols

The treatment of HAT depends on the stage at which the disease is diagnosed.

· Pentamidine in the hemo lymphatic phase

Pentamidine isethionate, an aromatic diamine, is the reference drug used for the treatment of early-stage HAT. Patients are hospitalised and receive 4 mg/kg of pentamidine in a daily intramuscular injection for 7 to 10 days.

· Melarsoprol in the meningo-encephalitic phase

The treatment of patients with late-stage disease involves the use of melarsoprol, a trivalent arsenical derivative requiring a more intense protocol and hospitalisation for 25 days. Melarsoprol has been used almost exclusively in the treatment of late-stage HAT for more than 40 years (10). The mode of action of melarsoprol is poorly understood. According to one generally accepted theory (although recently disputed), melarsoprol acts by depriving the trypanosome of trypanothion by binding irreversibly to it. Trypanothion, which is the analogue of glutathion in trypanosomes, protects the parasite from free radicals. The pharmacokinetic of melarsoprol is poorly understood, but it appears that the half-life of the drug is 35 hours. Melarsoprol crosses the blood-brain barrier in limited quantities (10,11).

In a common protocol with Melarsoprol, patients receive three series of three intravenous injections separated by rest periods of six days. The doses of melarsoprol are progressive, from 1.8 to 3.6 mg/kg/day. Prednisolone is combined systematically, as a preventive measure against reactive encephalopathy (12).

A continuous treatment schedule (2.16 mg/kg/day for 10 days) simplifying the protocol and reducing the hospitalisation period is currently under evaluation in several countries. Preliminary results show equivalent efficacy and similar safety to the standard therapeutic regimen (13).

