## Results and side effects of treatment with melarsoprol

In the late-stage disease, the cure rate after treatment with melarsoprol is estimated to be greater than 95% (10,11,14). The principal risk is that of reactive encephalopathy (5.9% of cases treated with melarsoprol in a series of 1083 patients in Zaire (15), with a high mortality rate (67.2% in the same series). In an Ivory Coast series with 350 patients (6), arsenical treatment was associated with minor side effects, such as isolated febrile episodes, pruriginous rashes and subcutaneous cellulitis, sometimes followed by necrosis at the injection site, in 11.4, 4.6 and 2.8% of cases, respectively.

MSF data from Adjumani in Northern Uganda provide the following figures: among 3110 late-stage patients treated with melarsoprol, 567 (18.2%) patients suffered side effects, including 194 (6.2%) cases of reactive encephalopathy. The lethality observed during treatment was 5.5% (170/3110). The lethality of reactive encephalopathies was 51.5% (100/194). The median duration of hospitalisation was 25 days (unpublished MSF data).

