## Side effects

In case of any side effect, the event will be recorded. The decision to withhold or to resume treatment will be left to the clinician in charge. Analysis will be done on an intention to treat basis.

The following definitions will be used for recording some of the side effects :

- Reactive encephalopathy: onset of a sudden or rapidly progressive episode of coma in a patient during treatment (Glasgow score less than or equal to 8) or status epilepticus.
- Arsobal reaction: tachycardia (pulse > 100 or 140 in children under 12 years of age), with fever > 38°C and conjunctival hyperaemia.
- Diabetes mellitus: fasting blood glucose greater than or equal to 1.3 g/l, associated with glycosuria.
- Cardiomyopathy: occurrence of an arrhythmia during treatment in a patient previously free from cardiovascular symptoms.
- Enteritis: occurrence of a diarrhoeic syndrome during treatment (three or more liquid stools per 24 hours, for three consecutive days or more) resistant to oral rehydration.

In case of occurrence of any manifestation that could lead to suspect imminent encephalopathy (severe headaches, conjunctival hyperaemia, high fever without a focus of infection or malaria parasites, isolated convulsion, behavioural disorders, etc.) the decision to withhold or to resume the treatment will be at the clinician’s discretion in accordance with the practices of the treatment centre.

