**3.7. Follow-up of patients**

**Table 2 : Timetable of activities during the study**

| **ACTIVITIES** | **D1** | **D2-11** | **D12** | **M6** | **M12** | **M24** | **Non-scheduled days** |
| --- | --- | --- | --- | --- | --- | --- | --- |
| **Informed consent– Inclusion** | X |  |  |  |  |  |  |
| **Randomisation** | X |  |  |  |  |  |  |
| **Clinical evaluation** | X | X | X | +/- | +/- | +/- | +/- |
| **Parasitological evaluation**  Woo  QBC  GP  LP | X  X  +/-  X |  | X  +/-  X | X  +/-  X | X  +/-  X | X  +/-  X | X  +/-  X |
| **Biological evaluation**  CSF white cells counts  Haematocrit Y  WBC count Y  Differential count Y | X  X  X  X |  | X  X  X  X | X | X | X | X |
| **Sampling for Antwerp study**  CSF sample collection  Serum sample collection | X  X |  | X  X | X  X | X  X | X  X | X  X |
| **Treatment**  Prednisolone *  A : Melarsoprol+nifurtimox  B : Melarsoprol+eflornithine  C : eflornithine +nifurtimox | X | X  X  X  X |  |  |  |  |  |
| **New therapeutic scheme if treatment failure** |  |  | X | X | X | X | X |

Y Only for the first 50 subjects

* Only for treatments A or B

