## Follow-up duration

Patients included in the study will be monitored for 24 months after the end of treatment.

Laboratory tests (lumbar puncture, glandular puncture, QBC, haematology) and clinical examinations will be undertaken at the end of hospitalisation and 6, 12 and 24 months after the end of the treatment.

A network of community health workers will ensure the presence of the patients included in the study at the 3 scheduled follow-up visits as far as possible. In addition, the address of each patient included in the study will be noted at the time of admission. Anyone missing a follow-up visit will be sent a reminder 3 times.

Apart from this, the patient will be allowed to come at any time in the trypanosomiasis treatment centre throughout the follow-up period.

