**4.2. Data to be collected**

*Demographic data:*

Name, age, sex, address, screening method (active or passive).

*Laboratory data on inclusion:*

Result of CATT whole blood and 1/4 dilution

Results of lymph node puncture (trypanosome +/‑)

Results of parasitological examination of the blood (WOO +/‑; QBC +/‑)

Results of parasitological examination of the CSF (trypanosome +/‑)

Spinal cell count

Haematology

*Clinical data on inclusion and during hospitalisation:*

Disease history

Weight/height on admission

Weight on discharge

Temperature

Lymph nodes

Neurological signs

Intercurrent disease

Treatment received and doses

*Side effects of treatment*

*Results of treatment*

*Laboratory data on discharge:*

Results of parasitological examination of the blood (QBC +/‑)

Parasitological examination of the CSF (trypanosome +/‑)

Spinal cell count

Haematology

Specific IgM in CSF and serum (Antwerp)

*Laboratory data during follow-up:*

Results of lymph node puncture (trypanosome +/‑)

Results of parasitological examination of the blood (QBC +/‑)

Parasitological examination of the CSF (trypanosome +/‑)

Spinal cell count

Specific IgM in CSF and serum (Antwerp)

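### Three side-effect definitions, including coma-type encephalopathy, stop at the end of treatment (D11), and the protocol states no consistent post-treatment window for the side-effect outcome

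*Protocol*

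**What the plan says.** Clinical safety shares the main objective with efficacy (section 2), and the proportion of side effects is the second outcome variable (section 3.8). Section 3.8 gives no period over which side effects are counted.

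The Side effects paragraph of section 3.6 opens with a general rule that any side effect is recorded, without an end date. It then defines five of them. Three are tied to the treatment period:

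- encephalopathy: "Reactive encephalopathy: onset of a sudden or rapidly progressive episode of coma in a patient during treatment", with status epilepticus as an alternative;
- cardiomyopathy: "occurrence of an arrhythmia during treatment in a patient previously free from cardiovascular symptoms";
- enteritis: "occurrence of a diarrhoeic syndrome during treatment".

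The Arsobal reaction and diabetes definitions carry no time limit.

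The treatment timetable (Table 1) ends on D11 in all arms: melarsoprol in A and B, nifurtimox in A and C. Eflornithine ends on D8. Patients stay in hospital for the treatment period, and no observation period after it is stated.

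In section 4.2, one list is headed "Clinical data on inclusion and during hospitalisation". The only list labelled for follow-up holds laboratory items. Side effects of treatment form a separate item with no period attached.

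In the timetable of activities (the first of two tables numbered 2), the evaluation row begins "Clinical evaluation | X | X | X" for D1, D2–11 and D12, and is then marked +/- at M6, M12, M24 and on non-scheduled days. Section 3.7, Follow-up duration, says instead that "clinical examinations will be undertaken at the end of hospitalisation and 6, 12 and 24 months after the end of the treatment".

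**The concern.** The protocol names encephalopathy as the principal risk of melarsoprol, and two of the three arms contain melarsoprol. Under the definition as written, a coma that starts after the last dose is not an encephalopathy, however typical it is. No fixed clinical evaluation falls between D12 and month 6, and the later ones are optional in one place and required in another. On a non-scheduled visit, blood and CSF tests are marked as required but clinical evaluation is not.

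Two people following the protocol could therefore classify the same late event differently, or not learn of it at all. The consequence falls on the second outcome variable and on the interim comparison of serious adverse reactions every hundred patients (Early stopping rules).

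**Working it through.** **1. Inputs**

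- Melarsoprol half-life: section 1.1, where "it appears that the half-life of the drug is 35 hours". The same section calls the drug's pharmacokinetics poorly understood.
- Nifurtimox half-life about 3 h and eflornithine 3.3 h: section 1.3.
- Encephalopathy on melarsoprol: 194 of 3110 local patients (section 1.1), or about 5% (Introduction).
- Group size: 145 (section 3.3).

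**2. The plan's own figures**

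194/3110 = 6.2%, as stated. 130/0.90 = 144.4, rounded up to 145 per group, as stated. Neither figure is in dispute.

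**3. Exposure after the definition closes**

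The fraction of the last-dose level remaining after t hours is 0.5^(t / half-life).

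- Melarsoprol at 24 h (D12): 0.5^(24/35) = 0.62.
- Melarsoprol at 72 h: 0.5^(72/35) = 0.24.
- Melarsoprol down to 5%: 35 × log2(20) = 151 h = 6.3 days, about D17.
- Nifurtimox at 24 h: 0.5^(24/3) = 0.004.
- Eflornithine has been stopped since D8.

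On the protocol's own half-lives, only melarsoprol exposure continues appreciably past D12. This describes drug level. It does not show when toxicity begins.

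**4. Cases at stake**

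Expected encephalopathies per melarsoprol arm: 145 × 6.2% = 9.0 (145 × 5% = 7.3 at the lower rate). These rates come from melarsoprol alone and may differ for the combinations. The share with onset after treatment is not in the documents, so it is varied here at the 6.2% rate:

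| Assumed late share | Cases not counted per arm | Rate counted |
| --- | --- | --- |
| 0% | 0 | 6.2% |
| 5% | 9.0 × 0.05 = 0.45 | 5.9% |
| 20% | 9.0 × 0.20 = 1.8 | 5.0% |
| 30% | 9.0 × 0.30 = 2.7 | 4.3% |

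**5. The passages side by side**

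| Place | What it fixes |
| --- | --- |
| Section 3.6, general rule | record any side effect, no end date |
| Section 3.6, three of five definitions | end with treatment (D11) |
| Section 3.8, second outcome | no window |
| Section 4.2, side-effect item | no period |
| Section 4.2, follow-up list | laboratory items only |
| Timetable of activities | clinical evaluation optional at M6, M12, M24 |
| Section 3.7, Follow-up duration | clinical examination at 6, 12 and 24 months |

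The last two rows contradict each other. The first two allow an event to be recorded but not classified.

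**The case against.** The strongest reply is that the protocol does not stop collecting side effects at D12. The general recording rule and the side-effect item in section 4.2 are open-ended. Two definitions have no limit, and one of them is the Arsobal reaction, which is specific to melarsoprol. Status epilepticus can be read as lying outside the treatment-period limit. Patients may come to the centre at any time. Deaths are assessed for causality over two years, and those judged likely due to treatment count as failures. With local lethality of encephalopathy at 51.5%, about half of any late cases would be fatal and could enter the primary outcome that way.

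All of this stands, so a reader who infers that late side effects are never collected goes beyond the text. It does not close the gap. Open-ended recording creates no contact between D12 and month 6. The death rule misses survivors, and deaths whose cause is unknown are excluded from the primary analysis. A recorded late coma still fails the definition.

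The reply also notes that a small loss would probably not reverse the encephalopathy comparison. If arm C had no cases, 9/145 against 0/145 gives Fisher p = 0.003, and 7/145 against 0/145 gives p = 0.015. That is fair, on the assumption of no cases in C.

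**Conclusion.** The definitions and the evaluation schedule need to be reconciled, and the side-effect outcome needs a stated window. The loss is small and uncertain: about 0.5 to 2 of roughly 9 expected encephalopathies per melarsoprol arm if 5–20% start after treatment, which is an assumption. It could be nil.

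Two stronger readings are tempting but not supported.

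- A reader might infer that the safety comparison as a whole is biased towards A and B and against C. The calendar window is the same in all arms, and the documents do not say when encephalopathy begins. Arm C also takes nifurtimox to D11; the protocol says its toxicity appears to rise with duration, so late nifurtimox effects in A and C could be missed too. The bias is plausible for encephalopathy only.
- A reader might infer that the new regimens will look safer than the local historical series because there "The median duration of hospitalisation was 25 days". That stay belongs to a longer course: three series of three injections with two six-day rests make 3 + 6 + 3 + 6 + 3 = 21 days. The historical lethality is also described as occurring during treatment, and section 3.8 plans comparisons between arms only.

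**What to change.** 1. In the Side effects paragraph of section 3.6, replace the limit to the treatment period with one stated window that extends past the last dose and is identical in the three arms. State the same window for the second outcome in section 3.8. Thirty days is an example; the documents do not single out a length, but the 6.3 days computed above argue against a window of only a few days.
2. In section 4.2, add side effects since discharge (type, onset date, outcome) to the follow-up data, taken at unscheduled visits and at M6. The onset date still allows an on-treatment count to be reported separately.
3. In the timetable of activities, change +/- to X for clinical evaluation at M6, M12 and M24 so that it agrees with section 3.7.

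The cost is wording in the protocol and the case-report form. The downsides are some recall error in onset dates and slightly higher side-effect rates. A status check near the end of the window through the existing community health workers would reduce recall error, but it is an added contact and the correction does not depend on it.

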## Patients withdrawal during the treatment

Patients will be withdrawn if :

- A deviation from treatments schedules is made by patients’ voluntary abandon.
- Exclusion criteria occurs at post-inclusion (see paragraph exclusion criteria in 3.2)

Patients will continue to receive the same treatment and follow-up will be done. These patients will be excluded from the analysis.

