**3.5. Randomisation**

Patients will be randomised on D1 (inclusion date), the day on which treatment is initiated. A fixed randomisation method will be used: the probability of being assigned one or other treatment will remain constant throughout the study.

The patients’ demographic, laboratory or clinical features might change during the study because of the control programme in progress. A blocking process in the randomisation will ensure that a comparable number of patients is included in each group at all times. The blocking procedure will not be disclosed to the field team before the end of the enrolment period.

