**3.8. Analysis**

This will be an "intention-to-treat" analysis. The treatment groups will be compared pair-wise.

The first outcome variable is the proportion of therapeutic failures in each treatment group.

The second outcome variable is the proportion of side effects occurring in each group.

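### The protocol promises an intention-to-treat analysis but removes randomised patients who abandon treatment or meet an exclusion criterion after inclusion, and defines no second analysis set

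*Protocol*

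**What the plan says.** The protocol states its analysis principle twice. Section 3.6, Side effects, leaves the decision to withhold or resume treatment after a side effect to the clinician and adds: "Analysis will be done on an intention to treat basis". Section 3.8, which governs the whole analysis, says: "This will be an 'intention-to-treat' analysis. The treatment groups will be compared pair-wise". It then names the primary outcome: "The first outcome variable is the proportion of therapeutic failures in each treatment group".

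Section 3.6, Patients withdrawal during the treatment, gives two grounds for withdrawal: "A deviation from treatments schedules is made by patients’ voluntary abandon" and "Exclusion criteria occurs at post-inclusion (see paragraph exclusion criteria in 3.2". It then rules: "Patients will continue to receive the same treatment and follow-up will be done. These patients will be excluded from the analysis".

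Section 3.5 fixes the timing: "Patients will be randomised on D1 (inclusion date), the day on which treatment is initiated". Whatever happens after inclusion therefore happens after randomisation.

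Two neighbouring rules bear on the same denominator. Section 3.7, Lost to follow-up, defines a drop-out only as someone who misses the 24-month visit. The Deaths paragraph excludes from the primary end-point analysis deaths whose link to treatment and to trypanosomiasis is unlikely or unknown.

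**The concern.** An intention-to-treat analysis keeps every randomised patient in the allocated group. The withdrawal rule takes some out because of events after allocation. An analyst who obeys one rule breaks the other, and the choice could be made once outcomes are known. A separate analysis plan could not settle this without departing from one of the two protocol statements.

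The exclusions cannot be assumed neutral. The trial is open, and section 5.1 concedes that lack of blinding does not guarantee uniform treatment across the groups. Table 1 shows very different burdens (one melarsoprol administration a day, tablets three times a day, four infusions a day), and section 1 describes different toxicities. Willingness to complete a course may therefore depend on the arm and be related to outcome. What is at stake is the protection that randomisation gives to the three pairwise comparisons. The information is also not missing: the withdrawal paragraph itself keeps these patients in follow-up.

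**Working it through.** **1. The rules side by side.**

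| Event after D1 | Section 3.6, Side effects, and 3.8 | Section 3.6, Patients withdrawal |
| --- | --- | --- |
| Clinician withholds treatment for a side effect | analysed | not listed, so analysed |
| Patient voluntarily abandons treatment | analysed (intention to treat) | followed up, excluded |
| Exclusion criterion met after inclusion | analysed (intention to treat) | followed up, excluded |

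Rows two and three conflict. Nothing elsewhere limits the exclusion to a secondary set. The withdrawal rule is not a proper per-protocol definition either, because patients whose treatment a clinician stopped remain in.

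**2. The plan's own figures.** Inputs from section 3.3: cure 95% against 85%, one-sided alpha 5%, power 80%, drop-out 10%.

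- Two-proportion formula: (1.645 × √(2 × 0.90 × 0.10) + 0.842 × √(0.95 × 0.05 + 0.85 × 0.15))² / 0.10² = 110.2.
- With continuity correction: (110.2 / 4) × (1 + √(1 + 4 / (110.2 × 0.10)))² = 129.5, so 130 per group, as stated.
- Drop-out: 130 / 0.90 = 144.4, so 145 per group, as stated.

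The allowance leaves 145 × 0.90 = 130.5 and does not mention withdrawals. If a further 2%, 5% or 10% of those randomised were excluded, 145 × 0.88 = 127.6, 145 × 0.85 = 123.3 or 145 × 0.80 = 116 would remain. This loss of numbers is the lesser matter: two one-sided tests with both true cure rates at 95% need 2 × 0.95 × 0.05 × (1.645 + 1.282)² / 0.10² = 81.4, so 82 per group. The issue is bias.

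**3. Size of the possible shift (illustration).** Let a share a of an arm be excluded, failing at rate f, while retained patients fail at rate r.

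- Failure over all randomised: (1 − a)r + af = r + a(f − r).
- Failure as analysed after exclusion: r.
- Shift in that arm: a(f − r).
- Net shift in the difference between arms 1 and 2: a₁(f₁ − r₁) − a₂(f₂ − r₂).

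The value r = 5% mirrors the 95% cure rate in section 3.3. The values of a and f are assumptions; the protocol gives none. With abandonment in one arm only:

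| a | f = 30% | f = 60% |
| --- | --- | --- |
| 1% | 0.01 × 0.25 = 0.25 points | 0.01 × 0.55 = 0.55 points |
| 5% | 0.05 × 0.25 = 1.25 points | 0.05 × 0.55 = 2.75 points |
| 10% | 0.10 × 0.25 = 2.5 points | 0.10 × 0.55 = 5.5 points |

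If both arms lose patients, the net shift is the difference of the two terms. It is zero when those terms are equal.

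**4. Direction.** Take a = 10% and f = 60% in arm 1 only.

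- If retained patients fail at 5% in both arms, the analysed difference is 0, while over all randomised patients it is 5.5 points. Exclusion favours equivalence.
- If retained patients fail at 5% in arm 1 and the comparator fails at 5 + 5.5 = 10.5%, the analysed difference is 5.5 points, while over all randomised patients it is 0. Exclusion works against equivalence.

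Nothing in the protocol says which pattern to expect.

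**The case against.** The strongest reply is that the rule reaches few patients and leaves the main tolerability route intact. Much of this stands.

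- **Toxicity.** A reader might infer that the rule strips out the patients who tolerated treatment badly. The documents do not support that in general: interruptions decided by the clinician stay in the analysis. Only a patient's own decision to stop triggers removal, and some of those decisions may follow poor tolerance.
- **Frequency.** Patients are inpatients throughout treatment (section 3.6, Treatment procedure), and section 5.1 relies on this for compliance. Abandonment may well be low, so the 1% row may be nearer the truth than the 10% row.
- **Late exclusion criteria.** Most items in section 3.2 are baseline facts (disease stage, earlier treated disease, weight, refugee status), more likely to be discovered late than caused by the arm. Pregnancy is the clearest that could newly arise. Loss of access to the centre is a poor example: the paragraph concerns the treatment period, and later losses fall under Lost to follow-up.
- **Direction.** A reader might infer a bias toward equivalence. Step 4 shows that this needs the arm with more abandonment also to be the one with more failures over all randomised patients, which the protocol does not establish.
- **Conservatism.** In an equivalence trial, intention to treat can itself favour equivalence, so a per-protocol view has value. That argues for reporting both sets, not for one undefined set labelled intention to treat.

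None of these points reconciles the two rules.

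**Conclusion.** The contradiction is established from the text and rests on no assumption: sections 3.6 (Side effects) and 3.8 promise intention to treat, while the withdrawal paragraph excludes followed-up, randomised patients, with no other analysis set defined. As written, post-randomisation events in an open trial can change the denominator of the primary outcome, so the protocol should be corrected.

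The size of the effect is unknown. Under the assumed values, with one arm affected, it runs from 0.25 to 0.55 points at 1% abandonment up to 5.5 points at 10%, against a 10-point margin for the difference. It is smaller when both arms lose similar patients, and its sign is not predictable. A reader might go further and infer that the rule could hide a difference larger than the margin. That would take, for example, 15% abandonment confined to one arm with no cures among them (0.15 × 0.95 = 14.3 points), and nothing in the protocol points to such a case.

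**What to change.** In section 3.6, Patients withdrawal during the treatment, replace the exclusion sentence with a statement that these patients are analysed in their allocated group in the primary intention-to-treat analysis, using the follow-up already planned. Use the two withdrawal grounds only to define a named, supportive per-protocol set, reported alongside the primary analysis, and consider whether the two sets agree before claiming equivalence. A formal requirement that both sets meet the margin would be an extra decision rule; resolving the contradiction does not require it.

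The new text should also say how it fits with the Deaths paragraph, which separately removes some deaths from the primary end-point analysis, and with missed 24-month visits under Lost to follow-up. Otherwise the primary denominator remains partly open.

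The cost is a short text change and one extra analysis. No new data are needed, and because the per-protocol set is supportive, the sample size need not change on this account.

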**Introduction**

*Trypanosoma brucei gambiense* (*Tbg*) Human African Trypanosomiasis (HAT) is a major public health problem in those areas in which it is currently rife (1). This is all the more so because the political upheavals, which disrupt the operations of the health services and cause population movements encourage the reappearance of historical foci (2,3). This disease, however, is still neglected and it is estimated that the control programmes cover only 10 to 20% of the 50 million people living in endemic regions (2).

HAT, which is consistently fatal in the absence of treatment, respond to a relatively non-toxic therapeutic agent, pentamidine(Pentacarinatâ), if the diagnosis is made at the hemo lymphatic phase (4). In the late stage of the disease, however, when the central nervous system is invaded by the parasite, use of arsenic derivatives such as melarsoprol (Arsobalâ) remains necessary. In about 5% of cases the use of melarsoprol causes iatrogenic encephalopathy, with a fatal outcome in up to 50%.

Eflornithine (difluoromethylornithine or eflornithine, Ornidylâ), for the time being, is the only other drug registered for the treatment of late-stage HAT. The institution of treatment regimens with eflornithine, however, is difficult because of the mode of administration of the product (1 infusion of 2 hours, every 6 hours). Actually, eflornithine is no longer available on the market but the patent is under supervision of WHO (5).

Nifurtimox (Lampitâ, Bayer), a product used in the treatment of Chagas disease, has only been tested empirically in HAT with contradictory results (4,6,7). This is a cheap drug, which is easy to administer (orally) but not registered for use in HAT. The type and frequency of side effects are poorly documented.

The available therapeutic spectrum for the treatment of late-stage HAT is therefore limited. Furthermore, the availability of the 3 drugs listed here is only guaranteed in the medium-term. Finally, signs of resistance to melarsoprol are beginning to appear in several areas (8,9).

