## Inclusion criteria

All patients suffering from *Tbg* HAT, with the following criteria:

- confirmed second-stage *T.b. gambiense* infection :
- Infection diagnosed parasitologically (blood or lymph node fluid) and white blood cells > 5/mm3 in cerebrospinal fluid (CSF)
- or Trypanosomes detected in the CSF [[1]](#footnote-2) with any CSF cell count
- and resident in the district
- and written consent of the patient or of one of the parents/guardians for children under 15 years of age.

The laboratory tests must have been carried out within the previous 14 days to be valid.

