***Exclusion criteria***

Any patients suffering from *Tbg* HAT admitted for treatment will be excluded from the study if one of the following criteria is met:

- Confirmed first-stage *T.b. gambiense* infection :
- Infection diagnosed parasitologically (blood or lymph node fluid) and trypanosomes not detected in the cerebrospinal fluid (CSF)
- and White blood cells £5/mm3 in CSF
- Second-stage *T.b. gambiense* infection :
- Trypanosome absent from blood (or lymph node fluid) and from CSF
- Or women pregnant on inclusion
- Or previous history of HAT confirmed treated during the last 24 months
- Or impossibility of regular access to the treatment centre during the 2 years following the end of the treatment
- Or less than 10 kg of body weight
- Or refugee patient

Patients diagnosed but non included in this protocol will be treated in accordance with the Uganda National Sleeping Sickness Control Programme protocols.

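### The withdrawal rule keeps every patient on the allocated combination whatever exclusion criterion arises after inclusion, with no exception for one re-staged as first-stage

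*Protocol*

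**What the plan says.** Section 3.6, under Patients withdrawal during the treatment, gives two grounds for withdrawal. One is voluntary abandonment of the schedule. The other reads "Exclusion criteria occurs at post-inclusion (see paragraph exclusion criteria in 3.2". For both, the instruction is "Patients will continue to receive the same treatment and follow-up will be done".

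The list it points to, in section 3.2, is mixed. Some entries have no bearing on which drug a patient should receive, such as refugee status or lack of regular access to the centre. Others do or may. Confirmed first-stage infection is defined there by parasites in blood or lymph node fluid "and trypanosomes not detected in the cerebrospinal fluid (CSF", together with a CSF white cell count of 5/mm3 or less. Pregnancy is listed as "Or women pregnant on inclusion".

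On drug choice, the Introduction describes the late stage as the point "when the central nervous system is invaded by the parasite, use of arsenic derivatives such as melarsoprol" becomes necessary. Section 1.1 names pentamidine as the reference drug for early-stage disease. Section 3.7 gives pentamidine to patients of any group in whom first-stage infection is identified during follow-up.

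**The concern.** The withdrawal rule is a positive instruction, and it treats all exclusion criteria alike. For refugee status or access, continuing a course already started is plainly right. For a patient whose stage is corrected to first-stage, the same words keep in place a regimen chosen for central nervous system disease, including an arsenical in two of the three groups.

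A patient recognised as first-stage before inclusion goes to the national programme's protocols (last sentence of the exclusion criteria in section 3.2). The same patient recognised afterwards would not. Care would then depend on when the stage was recognised. What is at stake is the treatment of that patient. The analysis set is a separate matter and is not raised here.

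**Working it through.** No figure in the plan bears on this point, so the check is a reading of the relevant sections against each other.

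1. **Does the rule reach first-stage disease?** The second withdrawal ground refers to the whole section 3.2 list without selection. Confirmed first-stage infection is on that list, so on its words the rule covers it.

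2. **Does another clause supply the exception?**
   - Section 3.6, Side effects: the clinician may withhold or resume treatment, but the clause is triggered by a side effect or by signs of imminent encephalopathy. A corrected stage is neither.
   - Section 3.7, Decisions in the event of infection during the follow-up: pentamidine for first-stage disease, but only for infection identified in follow-up.
   - Section 3.7, Classification of responses: the closing sentence leaves unclassifiable patients to the clinical staff, but it concerns response to treatment.
   - Section 3.2, last sentence: national protocols, but only for patients not included.

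   None covers a patient re-staged during treatment.

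3. **How could it arise?** Section 3.2 says of the qualifying tests: "The laboratory tests must have been carried out within the previous 14 days to be valid". The timetable in section 3.7 also places a lumbar puncture and "CSF white cells counts" on D1, and section 3.5 says "Patients will be randomised on D1 (inclusion date), the day on which treatment is initiated". No CSF test is scheduled on D2 to D11. The scheduled route is therefore a D1 result that is corrected after inclusion. It is narrower still because trypanosomes in the CSF qualify a patient at any cell count. Only patients who qualified on a count above 5/mm3 could be re-staged by a revised count.

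4. **Pregnancy.** No pregnancy test appears in the section 3.7 timetable or in the section 4.2 list of inclusion data, so a pregnancy already present may be recognised only later. The protocol gives no reason for this exclusion and no alternative regimen.

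5. **Exposure under a literal reading.** From Table 1 in section 3.6, for a correction made before the first study dose on D2:
   - melarsoprol (A and B): 10 days × 1.8 mg/kg = 18.0 mg/kg
   - eflornithine (B and C): 7 days × 4 = 28 infusions
   - nifurtimox (A and C): 10 days

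   The next scheduled CSF count, on D12, follows the last dose on D11. These figures restate the full course. They bound exposure and do not measure harm.

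6. **Can harm be estimated?** Section 1.1 reports reactive encephalopathy in 194/3110 = 6.2% of patients given melarsoprol, fatal in 100/194 = 51.5%. All were late-stage, and the treatment reported is melarsoprol rather than the trial combinations. The figures show that the drug's toxicity is serious. They give no excess risk for a first-stage patient in this trial.

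**The case against.** The strongest reply is about wording. The rule speaks of criteria that occur after inclusion, which fits access or refugee status better than an eligibility error. Pregnancy is defined at inclusion and cannot begin to apply later, and confirmed second-stage disease does not turn into first-stage disease during treatment. On that view the sentence was never meant for mis-staged patients. It also covers patients who abandon treatment, where it cannot be a literal order to dose, so it may be no more than a promise that leaving the study does not end care. This has force and lowers the weight of the point. It does not remove it, because the reference to section 3.2 is unrestricted and staff must act on the text as it stands. The written staff guideline promised in section 5.2 may say more, but it is not available here.

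Second, a reader might infer that the protocol allows randomisation before the stage is known and should fix the order of the CSF count and randomisation. The documents do not support that. Section 3.2 makes confirmed second-stage infection a condition of inclusion and takes the inclusion decision at admission on D1, so a qualifying result is already implied to come first.

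Third, a reader might infer that a pregnant patient would be safer off the combination. The documents do not show this. The disease is described as always fatal if untreated, the national alternative is not set out, and finishing a late-stage course may be the right choice.

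Fourth, a reader might see a direct contradiction with the pentamidine rules. Section 1.1 is background and the section 3.7 rule governs follow-up, so there is no clash of instructions for the same patient at the same time.

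**Conclusion.** The point holds as a minor one. The withdrawal rule is wider than its purpose needs. Taken literally, it keeps a patient re-staged as first-stage on a late-stage combination, against the protocol's own rationale for drug choice and without stated discretion to stop unless a side effect or suspected encephalopathy appears. For a pregnancy present on inclusion but recognised later, the conclusion goes no further than the absence of stated room for clinical judgement.

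This rests on two readings: that the same treatment means the allocated combination, and that a criterion recognised after inclusion falls under the rule. Cases should be rare. Neither their number nor any excess harm can be given from the protocol, and carrying the 6.2% encephalopathy rate over to these patients would not be justified.

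**What to change.** Add a provision to Patients withdrawal during the treatment in section 3.6:

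- Where an exclusion criterion bearing on drug choice or safety is recognised after inclusion, the clinician in charge may stop the allocated combination and treat under the national protocol, with pentamidine for confirmed first-stage disease.
- Borderline CSF counts stay with the clinician's judgement, so that no patient is under-treated through an automatic switch.
- A pregnancy present on inclusion and recognised later is likewise left to the clinician, with no presumption for or against stopping.
- Follow-up continues to 24 months in every case.

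For criteria without bearing on drug choice or safety, such as refugee status or access, the present rule can stand. The change is wording only. Its cost is that a few patients may not complete the allocated course.
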